## **5) Blind method**

In order to enhance the reliability of the results of this study and the conclusions derived

therefrom, on the basis of a comprehensive evaluation of the feasibility of the study, the random number table is sealed in a non-transparent envelope and will be kept by specially trained full-time personnel who are not involved in this experiment. Due to the characteristics of the operation itself, the operator could not implement the blind method. In this study, the patients and the personnel involve in data recording and collating will be blinded.

## **6) Trial content**

### **6.1 Drug and experimental equipment**

#### **6.1.1 Drugs**

Hydroxyethyl starch (Wanheng), SinopMA Approval number H81LK111, Specifications: 500 ml, Manufacturer: Beijing Fresenius Kabi Pharmaceutical Co., LTD

Sodium Potassium Magnesium Calcium Glucose Injection (LEjia), SINopMA approval number H180514EN, specifications: 500 ml, Manufacturer: Jiangsu Hengrui Pharmaceutical Co., LTD

Compound Sodium Chloride injection, SINopOL H191536LK, specification: 500 ml, Manufacturer: Hubei Yichang Renfu Pharmaceutical Co., LTD

Anbijie Medical ultrasonic coupler (Anxinchao), Chongqing Food and Drug Administration (standard) word 2014 No. 2230176

Lidocaine hydrochloride injection, Sinopharm approval number H22020052, specification: 5 ml, Manufacturer: Jilin Kangnaier Pharmaceutical Co., LTD

#### **6.1.2 Equipment**

Disposable sterile single cavity/double cavity central venous catheter kit (Abel), manufacturer: Guangdong Baihe Medical Technology Co., LTD

Disposable aseptic protective sleeve, manufacturer: Guangzhou YAFu Biotechnology Co., LTD

Monitor, manufacturer: Royal Philips, Netherlands

Mindray M9T notebook color channel ultrasonic diagnostic system, manufacturer: Shenzhen Mindray Biomedical Electronics Co., LTD

## **6.2 Operation Method**

### **6.2.1 Method of anesthesia**

Noninvasive blood pressure, electrocardiogram, heart rate and pulse oxygen saturation will be routinely monitored after all patients enter the catheter preparation room in the operating room. Peripheral veins will be opened. Right internal jugular vein puncture catheterization will be performed under local anesthesia.

### **6.2.2 Puncture and image acquisition protocol**

All right internal jugular vein puncture catheterization procedures will be performed by the same senior attending physician who is proficient in both methods. A one-man technique will be used (the same operator operated the ultrasound probe and puncture needle) using the 12L5-A high frequency probe of the Mindray M9T notebook color ultrasound diagnostic system with a probe length of 4.7cm (set frequency 7.5-10 MHz and depth of 5cm). After the patient be anesthetized, the pillow will be removed and the patient lay flat with the head tilted 30 degree to the left and the head low and the foot high at 15 degree. Before preparing for skin disinfection, preoperative ultrasound examination will be performed to identify IJV and CCA in the images (generally IJV is shallower than CCA, the vessel wall is thin, the diameter is thick, the lumen is oval, the size can change with breathing, and the probe can be pressed flat; CCA position is deep, the blood vessel wall is thick, the diameter is thin, the lumen is round, and the probe pressure can not squish it. Color Doppler ultrasound imaging technology will be used, and the probe will be oriented towards the proximal end. It could be seen that the red blood flow signal area is CCA, while the blue blood flow signal area is IJV), patency of the internal jugular vein. The adjacent relationship between IJV and CCA in the short axis plane and oblique axis plane of all patients will be observed at the thyroid cartilage level, and ultrasound images will be collected and saved.

After the images be saved, the modified combined short and long axis method and oblique axis method will be performed according to the group conditions. First, routine disinfection will be performed, sterile tissue will be laid, the ultrasonic probe will be put into the sterile protective cover, and 10 ml of sterile ultrasonic coupling agent will be injected into the protective cover, and the probe cover will be fixed. In the modified combined short and

long axis method, ultrasonic probe will be fixed the radiopaque barium line at the center line of the probe in advance. The two groups of operation methods are as follows:

Group M (modified short-axis combined long-axis method) : The ultrasound probe will be placed transversally at the apex of the right sternocleidomastoid triangle (the triangle formed by the lower end of the sternocleidomastoid and the pectoral bone and the superior margin of the clavicle) (parallel to the clavicle), with the probe Mark With the point facing inwards of the patient, a short-axis view of the IJV and CCA can be observed. Adjust the left and right positions of the probe so that the acoustic shadow of the probe barium line falls just above the IJV midpoint. After local anesthesia, the puncture needle enters the needle from outside the probe midpoint plane, and stops entering the needle when a high-echo bright spot is seen on the ultrasound screen. Rotate the ultrasound probe 90 degree clockwise, that is, the IJV long-axis section and the puncture needle body can be seen. When the needle tip is seen in the ultrasonic image punctured the blood vessel wall and there is dark red blood flow back to the syringe, stop the needle, stop the ultrasonic exploration, insert the guide wire, ultrasonic short axis to confirm the correct position of the guide wire, insert the central venous catheter, draw back dark red blood to confirm the central venous catheter is placed in the internal jugular vein, fix the catheter, cover the sterile transparent patch.

Group O (oblique axis method) : The ultrasound probe will be placed transversally at the apex of the right sternocleidomastoid triangle (the triangle formed by the lower end of the sternocleidomastoid, the thoracic bone and the superior margin of the clavicle) (parallel to the clavicle), and the probe Mark point will be toward the patient's inner side, and the short axis view of IJV and CCA could be observed. Then the probe was rotated 45 degree clockwise so that the Mark point of the probe was facing the patient's contralateral nipple at the proximal end, that is, the IJV oblique axis plane will be obtained. After local anesthesia, the puncture needle was inserted into the plane 0.5 ~ 1cm from the outside of the probe, and the process of the puncture needle will be observed in real time during the puncture process. When it is seen in the ultrasound image that the needle tip punctured the blood vessel wall and dark red blood returned to the syringe smoothly, the needle insertion will be stopped, and then the guide wire will be placed, the ultrasound short axis again confirmed the correct position of the guide wire, the central venous catheter was placed, the dark red blood be drawn back to confirm the

central venous catheter be placed in the internal jugular vein, the catheter will be fixed, and the sterile transparent paste will be covered.

### **6.2.3 Preplan and treatment plan for complications of puncture**

#### **1) Allergic reactions cause by local anesthesia drugs and fluids used during the study.**

We will strictly screen patients, ask about drug allergy history and family history in detail, and prepare allergy rescue drugs and equipment. In the event of an allergic reaction, stop the medication immediately. For mild allergic reactions, give anti-allergy medication; In case of severe anaphylaxis, initiate the severe anaphylaxis emergency plan.

#### **2) Risks associated with central venipuncture:**

The most common adverse reactions are mild local bleeding and pain at the acupuncture site. Swelling under the skin and containing blood (hematoma), etc., can be treated by local compression, adding local anesthetic drugs and other measures; Rare but serious adverse reactions include infection, pneumothorax, hemothorax, arterial injury, brachial plexus injury, thyroid injury, chylorrhea, puncture failure, etc. Strict aseptic disinfection can be performed by selecting experienced operators, gentle operation, adjusting ultrasound equipment parameters, and clearly displaying important tissue structures around the internal jugular vein. If the patient encounter puncture difficulties or failure, the operation should be terminated in time, and the patient will be identified as puncture failure and withdrawn from the study. Doctors with higher experience will be invited to change the puncture site. If relevant complications are suspected, the physician can confirm the relevant complications in time through clinical physical examination, combined with ultrasound and impact examination, and conduct timely treatment and treatment.

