## **7) Outcome indicators**

### **7.1 primary outcome indicator**

① Successful first needle pass without posterior vessel wall puncture (PVWP). Insertion of the puncture needle into the IJV with no blood aspirated during aspiration, but visible blood return upon withdrawing the needle, which can be regarded as PVWP.

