## 7.2 Secondary outcome indicator

① IJV insertion time, define: from the beginning of needle insertion to ultrasound confirmation that the guide wire be in the IJV and in the correct position. ② Total puncture time, defined: from the beginning of needle insertion to catheter fixation, and the position is correct. ③ IJV transverse diameter, CCA and IJV overlapping rate ([IJV and CCA overlapping distance /CCA transverse diameter] x 100%), safe puncture distance =IJV transverse diameter - IJV and CCA overlapping distance, CCA and IJV relative position relationship. ④ The number of punctures (each time the puncture needle recedes and adjusts the direction is regarded as a puncture). ⑤ The total success rate of puncture (puncture times >3 or complications are regarded as failure, and other central veins are replaced to complete puncture catheterization). ⑥ Puncture complications, such as hematoma, mispuncture artery, external jugular vein injury, thyroid injury, nerve injury, pneumothorax and hemothorax, etc. (combined with the puncture operator, puncture operation video and imaging data to determine the judgment of pneumothorax and hemothorax by experienced imaging doctors according to the chest film to judge).

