## 8) Statistical analysis

### 8.1 Sample estimation

We assume a first pass without PVWP rate of 95% and 90% for the MCSL and OA-IP methods, respectively. The non-inferiority bound is pre-set as a primary outcome difference between groups of -8%. We estimate that 85 patients in each group would provide 90% of the power at the 0.025 level to compare the MCSL approach with the OA-IP approach. Considering the 10% shedding rate, ultimately, we intend to enroll 95 patients in each group.

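### Protocol 6.2.3 withdraws patients whose puncture is difficult or fails, although they are known outcome failures; if withdrawal is applied as exclusion, failures leave the denominator

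*Protocol*

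**What the plan says.** - Protocol 6.2.3, item 2 (risks of central venipuncture) gives the trigger: "If the patient encounter puncture difficulties or failure, the operation should be terminated in time". It then gives the consequence: "the patient will be identified as puncture failure and withdrawn from the study". No number of attempts or other threshold defines difficulty there.
- Protocol 7.1 makes the primary outcome binary: "Successful first needle pass without posterior vessel wall puncture (PVWP)".
- Protocol 7.2, item 5 defines the total success rate: "puncture times >3 or complications are regarded as failure, and other central veins are replaced to complete puncture catheterization".
- Protocol 8.1 sets the comparison: "We assume a first pass without PVWP rate of 95% and 90% for the MCSL and OA-IP methods, respectively". It also sets the margin: "The non-inferiority bound is pre-set as a primary outcome difference between groups of -8" percentage points. It ends: "Considering the 10% shedding rate, ultimately, we intend to enroll 95 patients in each group". It does not say which losses count as shedding.

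**The concern.** The reason for withdrawal in 6.2.3 is not an unrelated loss. A puncture abandoned as failed is a non-success on the primary outcome, and 7.2 counts the same course of events as a failure. One section therefore takes the patient out of the study while another needs that patient in the denominator.

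If staff or analysts take withdrawal to mean exclusion, both observed success rates move towards 100%. When the experimental method is truly worse and the same share is withdrawn in each arm, the gap between arms shrinks, so a method at the non-inferiority limit is more likely to pass. Withdrawal taken literally may also end the collection of times and complications in these patients, and no later analysis can recover those data.

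**Working it through.** **1. The plan's own figure.** Inputs from Protocol 8.1: rates 0.95 (MCSL, group M) and 0.90 (OA-IP, group O), margin 0.08, level 0.025 (taken as one-sided), power 90%.

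n = [0.95×0.05 + 0.90×0.10] × (1.960 + 1.282)² / (0.05 + 0.08)² = 0.1375 × 10.507 / 0.0169 = 85.5 per group.

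The protocol states 85, at which power is 89.8%. Allowing for 10% loss, 85/0.90 = 94.4, rounded up to 95. The stated figures reproduce, and this point does not affect them.

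**2. What exclusion does to a rate.** Let p be the true success rate and f the share of non-successes excluded. The expected observed rate is p / [1 − f(1 − p)]. The documents give no f, so it is an assumption shown over a range.

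With true rates at the margin (M 0.82, O 0.90) and f = 0.25:
- M: 0.82 / (1 − 0.25×0.18) = 0.82/0.955 = 0.859
- O: 0.90 / (1 − 0.25×0.10) = 0.90/0.975 = 0.923
- Difference: −6.4 points instead of −8.0

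**3. What it does to the error rate.** This was simulated with 85 randomised per arm, true rates 0.82 and 0.90, and the same f in both arms. Non-inferiority is declared when the lower limit of the two-sided 95% Newcombe interval for M − O lies above −8 points. The interval method is also an assumption, since the protocol names none for this comparison.

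| Share of non-successes excluded (f) | Expected difference (points) | False non-inferiority |
|---|---|---|
| 0 | −8.0 | 2.4% |
| 10% | −7.4 | about 3% |
| 25% | −6.4 | about 5% |
| 50% | −4.6 | about 10% |
| 75% | −2.5 | 28% |

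**4. Sensitivity to method.** A Wald interval with 95 per arm gives 3.0%, 6.2%, 16.0% and 48.9% for f = 0, 25%, 50% and 75%. The direction is the same and the rise is steeper.

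**5. Sensitivity to unequal exclusion.** True rates at the margin, 95 per arm:
- Half of O failures and a quarter of M failures excluded: expected difference −8.9 points; false non-inferiority 1.5% (Newcombe) or 2.1% (Wald), below nominal.
- A quarter of O failures and half of M failures excluded: −2.2 points; 25% (Newcombe) or 30% (Wald).

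**6. At the planned rates (95% v 90%), equal f.** The expected difference falls from +5.0 to +3.9, +2.7 and +1.4 points for f = 25%, 50% and 75%. The chance of declaring non-inferiority rises from 93.7% to 94.8%, 96.7% and 99.0% (Wald, 95 per arm). The estimate moves against the new method while the non-inferiority claim becomes easier.

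**The case against.** The strongest reply is that the protocol never says these patients leave the denominator. The sentence first labels the patient a puncture failure, it stands in a section on managing complications, and 7.2 counts the same course of events as a failure. On that reading, withdrawal only ends the study procedure. Analysis sets are commonly left to an SAP, which is not shown. This stands as far as it goes: a reader might infer that the protocol removes failures from the analysis, and the text does not establish that. It does not rescue the wording, because the point is an instruction the protocol gives, not a missing definition. An SAP cannot restore data that were not collected because a patient was withdrawn.

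Three further limits also stand.

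- **The share is probably well below 1.** A PVWP, or success on the second or third pass, is a primary non-success that need not trigger 6.2.3, and that section lists puncture failure among rare events. Low shares are plausible, and the larger error rates need half or more of all non-successes to be excluded. With difficulty left undefined, no value can be fixed.
- **The direction is conditional.** A reader might infer that the bias always favours non-inferiority. Step 5 shows that it can reverse when mainly control failures are withdrawn. The single operator is unblinded (6.2.2 and section 5), so unequal withdrawal cannot be ruled out.
- **The 10% shedding is not evidence of planned removal.** A reader might infer that it stands for failed punctures, because a one-session procedure has few other losses and 10% equals the assumed control failure rate. The documents do not support this. Section 4 places consent and enrolment on the day before surgery, while 6.2.2 describes the ultrasound check of the vein only just before the procedure. An absent vein, thrombosis or unclear imaging can therefore surface after enrolment, and surgery may be cancelled. The same 10% is applied to group M, whose assumed failure rate is 5%.

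**Conclusion.** The point holds in conditional form. Sections 6.2.3, 7.1 and 7.2 do not fit together: a patient with a known non-success is told to leave the study, while the outcome definitions need that patient counted. If withdrawal is applied as exclusion, with equal shares in both arms and true rates at the margin, the false non-inferiority rate exceeds its 2.4% baseline at every share tabulated, from about 3% at 10% to 28% at 75%.

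Those figures rest on assumed shares, an assumed interval method and equal withdrawal. They show what the wording exposes the trial to and do not predict what will happen. The wording bears directly on the primary conclusion and costs little to correct, so it should be corrected.

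**What to change.** - **Section 6.2.3, item 2:** replace the withdrawal clause with wording to this effect: the study puncture ends; the patient stays in the study and in the analysis as randomised, scored as non-success for the primary outcome and as failure for the total success rate; data collection continues.
- **Section 8.1:** state that patients with a difficult or failed puncture do not count towards the 10% shedding.

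The clinical handling of a failed puncture stays as written, and the sample size is unaffected. The cost is two short text changes and slightly lower observed success rates. How the two time outcomes treat these patients is a separate analysis choice that this change does not settle.

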## **7) Outcome indicators**

### **7.1 primary outcome indicator**

① Successful first needle pass without posterior vessel wall puncture (PVWP). Insertion of the puncture needle into the IJV with no blood aspirated during aspiration, but visible blood return upon withdrawing the needle, which can be regarded as PVWP.

## 7.2 Secondary outcome indicator

① IJV insertion time, define: from the beginning of needle insertion to ultrasound confirmation that the guide wire be in the IJV and in the correct position. ② Total puncture time, defined: from the beginning of needle insertion to catheter fixation, and the position is correct. ③ IJV transverse diameter, CCA and IJV overlapping rate ([IJV and CCA overlapping distance /CCA transverse diameter] x 100%), safe puncture distance =IJV transverse diameter - IJV and CCA overlapping distance, CCA and IJV relative position relationship. ④ The number of punctures (each time the puncture needle recedes and adjusts the direction is regarded as a puncture). ⑤ The total success rate of puncture (puncture times >3 or complications are regarded as failure, and other central veins are replaced to complete puncture catheterization). ⑥ Puncture complications, such as hematoma, mispuncture artery, external jugular vein injury, thyroid injury, nerve injury, pneumothorax and hemothorax, etc. (combined with the puncture operator, puncture operation video and imaging data to determine the judgment of pneumothorax and hemothorax by experienced imaging doctors according to the chest film to judge).

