## **2. Objective of the study**

To evaluate the safety and effectiveness of modified combined short and long axis technique in right internal jugular vein puncture, compare the difference between it and oblique axis method in puncture success rate and puncture complications, find the most suitable method for right internal jugular vein puncture in obese patients, and promote the technology to improve the regional medical technology level.

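### Secondary item 5 counts any complication as a failed puncture, so total puncture success is an unlabelled composite and the placement success rate cannot be isolated

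*Protocol*

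**What the plan says.** The objective (section 2) names two comparisons between the methods: "compare the difference between it and oblique axis method in puncture success rate and puncture complications".

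Section 7.2 turns these into secondary outcomes. Item 4 is the number of punctures. Item 5 is the total success rate, defined through its failures: "puncture times >3 or complications are regarded as failure, and other central veins are replaced to complete puncture catheterization". Item 6 is a separate outcome: "Puncture complications, such as hematoma, mispuncture artery, external jugular vein injury, thyroid injury, nerve injury, pneumothorax and hemothorax, etc". Neither item 5 nor item 6 grades severity or sets a time window.

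The primary outcome (section 7.1) requires success on the first needle pass with no posterior vessel wall puncture (PVWP). No other complication enters it.

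Section 6.2.3, part 2, describes haematoma as an event managed locally: "Swelling under the skin and containing blood (hematoma), etc., can be treated by local compression, adding local anesthetic drugs and other measures". On puncture difficulty or failure, the same part says the procedure is stopped, "the patient will be identified as puncture failure and withdrawn from the study", and a different puncture site is used.

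**The concern.** A reader will take a total success rate to mean the share of patients whose catheter was placed in the intended vein within the allowed attempts. Item 5 measures something else: placement within 3 punctures and free of any complication. Three consequences follow.

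- The same patient can be a success on the primary outcome and a failure on item 5, although item 5 allows more punctures.
- A difference in item 5 between the arms may reflect minor local events and not placement. The same events are reported again under item 6.
- The clause about another central vein does not fit a catheter that is already correctly in place. It also sits badly with the local treatment of haematoma in section 6.2.3.

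At stake is how the success-rate half of the objective is read. The primary test is not involved.

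**Working it through.** **Inputs from the protocol**
- Failure in item 5: more than 3 punctures, or complications (section 7.2).
- Haematoma is a listed complication with no grade (section 7.2, item 6).
- The primary outcome excludes only PVWP (section 7.1).
- Assumed rates of first pass without PVWP: 95% for the modified combined method (M) and 90% for the oblique axis method (O) (section 8.1).
- No complication rate and no total success rate are given anywhere.

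**Step 1. The plan's own figure.** Item 5 has none. The only computed figure is the sample size for the primary outcome, with margin -8% and 0.025 taken as one-sided:

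n = (1.960 + 1.282)² × (0.95 × 0.05 + 0.90 × 0.10) / (0.05 + 0.08)² = 10.51 × 0.1375 / 0.0169 ≈ 85.5, so 86 per group.

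The plan states 85, at which power is 89.8%; 85 / 0.90 = 94.4, so 95 per group. The plan's figure is reproduced to within one patient and does not depend on item 5.

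**Step 2. One patient under each definition.** Take a right IJV catheter placed on the first pass, no PVWP, and a small haematoma treated locally.
- Primary outcome: success.
- Item 4: one puncture.
- Item 5, literal reading: failure, because a complication occurred.
- Item 5, narrow reading (only complications that led to another vein count): success, because no other vein was used.
- Item 6: one complication under either reading.

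The two readings of item 5 classify the same patient differently, and the text does not choose between them.

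**Step 3. Size under the literal reading (illustration).** Let s be the proportion placed in the right IJV within 3 punctures, and c the proportion with a complication among those placed. Then

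item 5 success = s × (1 − c), and with equal s the difference between arms = s × (c_O − c_M).

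Assume s = 98% in both arms, so the true placement difference is 0.

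| Assumed c, M versus O | Item 5, M | Item 5, O | Apparent success difference |
|---|---|---|---|
| 0% versus 0% | 98.0% | 98.0% | 0 points |
| 2% versus 5% | 0.98 × 0.98 = 96.0% | 0.98 × 0.95 = 93.1% | 2.9 points |
| 2% versus 10% | 96.0% | 0.98 × 0.90 = 88.2% | 7.8 points |
| 5% versus 15% | 0.98 × 0.95 = 93.1% | 0.98 × 0.85 = 83.3% | 9.8 points |

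With 95 patients per arm, the 7.8-point row is 95 × 0.0784 ≈ 7.4 patients. In that row the O arm's 88.2% also lies below the 90% assumed in section 8.1 for first pass without PVWP, although 98% of catheters are in the intended vein.

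**Step 4. With complications removed from the definition,** or under the narrow reading with the same placement rates, item 5 equals s in each arm and the difference is 0 in every row.

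**The case against.** The best defence reads item 5 as a whole: a failure is an attempt abandoned, for too many punctures or for a complication, and completed through another vein. Section 6.2.3 partly fits this, since it links failure to stopping and changing site. On that reading the haematoma example is not a failure and the apparent differences vanish. The reading is possible, but item 5 does not state the change of vein as a condition, and two defensible readings give different failure counts. This supports clarifying the definition.

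It can also be said that a composite of uncomplicated success, prespecified, identical in both arms and with its components reported in items 4 and 6, is legitimate. That stands. The difficulty is that it carries the name of a success rate, while no outcome gives plain placement success.

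Some stronger inferences are not supported:
- That success and complications cannot be compared separately. Item 6 reports complications alone, and item 4 and the primary outcome both inform on success.
- That the protocol ranks haematoma among the most common reactions. Section 6.2.3 says so only of mild local bleeding and pain; haematoma comes next, as a treatable event with no frequency given, and nothing is said there about the vein.
- That the 95% in section 8.1 is plain first-pass success. It is first pass without PVWP, so the other 5% cannot be taken as successes on the second or third pass.

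**Conclusion.** The point holds for item 5 only. As worded, it makes complications of any severity a failure. It overlaps item 6, can contradict the primary outcome for the same patient, and can produce a success difference with no difference in placement. The placement success rate cannot be isolated from it.

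The illustrated distortion is 2.9 to 9.8 points. It rests on an assumed 98% placement in both arms, on assumed complication rates, and on the literal reading. It is zero if complications are equally frequent among placed catheters in the two arms, or if the narrow reading was meant. A reader might infer that the trial's main conclusion is at risk. It is not: the primary outcome, the -8% margin and the 85 and 95 per group do not use item 5. The correction should be made, but it concerns one secondary outcome.

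**What to change.** 1. Define total puncture success as a catheter confirmed in the right IJV within the protocol's own limit of 3 punctures, whatever complications occurred.
2. Use all randomised patients as the denominator, including those whom section 6.2.3 withdraws as puncture failures, so that failures are not lost from the rate.
3. Report complications under item 6. If a complication-free measure is wanted, add it as a separately named outcome, for example uncomplicated success.
4. Reconcile the change-of-vein clause in item 5 with section 6.2.3, and state whether that clause is a condition for failure or a description of what follows it. How such patients are managed is for the investigators to settle.

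The cost is one reworded definition. Puncture number and complications are already outcomes, and the group procedures in section 6.2.2 already confirm catheter position, so no new data are needed. The downside is that placement success may sit near its ceiling in both arms and separate them poorly. The primary analysis and sample size stay as they are.

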## **3. Research Scheme**

## **1) Research design**

This is a single-center, randomized, controlled, non-inferiority, evaluator blind clinical study. The modified combined short and long axis method will be selected as the experimental group and the inclined axis method as the control group, and 190 subjects will be planned to be included in the study according to 1:1 balanced allocation.

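### The trial is called evaluator blind, but no blinded outcome assessor is named, and the unblinded operator and the procedure video are listed as sources for judging complications, which also feed total success

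*Protocol*

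**What the plan says.** Protocol, section 3, 1) Research design: "This is a single-center, randomized, controlled, non-inferiority, evaluator blind clinical study".

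Protocol, 5) Blind method: "Due to the characteristics of the operation itself, the operator could not implement the blind method". The same section lists who is blinded: "the patients and the personnel involve in data recording and collating will be blinded". Nobody who judges outcomes is on that list.

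Protocol, 6.2.2: all procedures "will be performed by the same senior attending physician who is proficient in both methods".

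Protocol, 7.2, item 6, on deciding complications: "combined with the puncture operator, puncture operation video and imaging data to determine the judgment". The sentence runs straight on to pneumothorax and haemothorax, which experienced imaging doctors judge from the chest film.

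Protocol, 7.2, item 5, on total success: "puncture times >3 or complications are regarded as failure".

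**The concern.** An evaluator-blind label tells a reader that whoever decides an outcome does not know the technique used. For complications, the protocol names a source who always knows it (the operator) and a second source that very probably reveals it (the video). It names no one who decides without knowing.

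Three features make this more than a label problem. One physician performs every procedure, so any preference for one method would be systematic and would not average out across operators. Section 6.2.3 places haematoma with the minor reactions, and no size or threshold is given, so whether one is counted is open to judgment. And one judgment enters two endpoints, because item 5 makes a complication a total-success failure. Section 2 names puncture success and complications as what the study sets out to compare.

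**Working it through.** **The plan's own figure.** The only calculation in the protocol is the sample size for the primary outcome (section 8.1: 95% and 90%, margin 8 points, 0.025 taken as one-sided, 90% power).

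- n = [0.95×0.05 + 0.90×0.10] × (1.960 + 1.282)² / (0.05 + 0.08)² = 0.1375 × 10.507 / 0.0169 = 85.5 per group, against 85 stated. Power at 85 is 89.8%.
- With 10% dropout: 85 / 0.90 = 94.4, rounded up to 95 as stated.

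The figure reproduces to within rounding. Nothing below depends on it or changes it.

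**The sections side by side.**

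| Question | Where | Answer in the protocol |
|---|---|---|
| Is the evaluator blind? | 1) Research design | Yes |
| Is the operator blind? | 5) Blind method | No |
| Who is blinded? | 5) Blind method | Patients; staff who record and collate data |
| What informs the judgment of complications? | 7.2, item 6 | Operator, operation video, imaging data |
| Who reads for pneumothorax and haemothorax? | 7.2, item 6 | Imaging doctors, from the chest film; masking not stated |
| Where do complications go next? | 7.2, item 5 | Into total success, as failures |

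**Step 1: how item 6 can be read.** Its wording allows two readings.

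- *Reading A (likelier):* operator, video and imaging together settle complications in general, and imaging doctors settle pneumothorax and haemothorax. Haematoma, arterial puncture, and external jugular vein, thyroid and nerve injury are then judged with unblinded input.
- *Reading B:* the whole parenthesis concerns pneumothorax and haemothorax. The operator is then a source even for these, and the other complications have no stated assessor.

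Neither reading yields a blinded assessment of the other complications.

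**Step 2: does the video show the arm?** The protocol does not say what the video frames, so this is an inference, though a strong one. Under 6.2.2, group M turns the probe 90 degrees after the needle has entered and has a barium line fixed to the probe. Group O turns it 45 degrees before needling and watches the needle throughout. Nothing says that the video is masked or edited.

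**Step 3: do the blinded data staff close the gap?** No. They record and collate judgments already formed with the operator's input.

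**Step 4: does 6.2.3 supply a blinded assessor?** No. It has the physician confirm suspected complications by physical examination with ultrasound and imaging, and does not say that this physician is unaware of the group.

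**The case against.** The strongest reply has four parts.

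*The operator is a source, not the one who decides.* This stands. A reader might infer that the operator grades the harms of the operator's own procedures. The text says only that the operator is combined with other sources. Facts reported by the operator and weighed by someone else would also fit it. What remains is that the person who weighs them is neither named nor said to be blind.

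*The sentence is ambiguous.* This also stands, and it is why both readings are set out. The ambiguity does not rescue the label, because neither reading gives a blinded evaluator.

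*There are other checks.* Examination, ultrasound and imaging under 6.2.3 limit how freely an event could be missed or dismissed. They are a real restraint, but they are not blinding.

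*The reach is limited.* The operator's status is openly disclosed, the endpoints are secondary, and the sample size, margin and definition of the primary outcome are untouched. All of this is true. It lowers the weight of the point without removing the contradiction.

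**Conclusion.** The protocol claims a property that it does not provide for these endpoints. Complications other than pneumothorax and haemothorax are either judged with unblinded input or have no stated assessor, and total success inherits this. The contradiction rests on the text alone. The one inference is that the video shows the technique.

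The size and direction of any bias cannot be computed, because the document gives no complication rates and nothing about misjudgment. A reader might try to put a number on it as true rate × share of events under-called in one arm. With assumed rates of 5–15% and 20–40% under-called, this gives 0.05×0.2 = 1 point to 0.15×0.4 = 6 points. With assumed rates of 1–3%, it gives 0.01×0.2 = 0.2 to 0.03×0.4 = 1.2 points. The result simply follows the assumption, so neither range is an estimate.

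Two further inferences are also unsupported. A complication not called does not shift total success one for one: a patient with more than 3 punctures fails anyway, so one for one is only the upper limit. The 8-point margin is no yardstick here, since it was set for the primary outcome and no margin exists for complications or total success.

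The point deserves correction before results are reported as evaluator blind. It does not threaten the primary analysis.

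**What to change.** In 7.2, item 6:

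- Have the operator record observed facts only, and not decide whether a complication occurred.
- Have the imaging doctors already named read chest films and saved imaging without the group label.
- Keep the operation video as a source, since it is a check on the operator's account, but state that judgments using it are not blinded.
- Repair the sentence so that it is clear which sources apply to which complications.

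In section 3, 1) Research design and 5) Blind method, limit the evaluator-blind claim to the chest-film and imaging readings and to data recording and collating. State that complications judged from the procedure, and total success, are not assessed blind and will be interpreted as such.

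Replacing the full video with clips from guide-wire confirmation onward would not achieve masking. Only group M has the barium line on the probe, and its shadow appears in the short-axis view. For the same reason, removing the group label does not by itself mask ultrasound frames recorded during a group M procedure. Any reading that relies on such frames belongs with the unblinded judgments.

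The cost is protocol wording and removing group labels from stored images. The downside is a narrower blinding claim, and events during the procedure still rest on unblinded information.
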